## Abstract

**Background:**

Obsessive–compulsive disorder (OCD) is a neuropsychiatric disorder which often proves refractory to current treatment approaches. Transcranial direct current stimulation (tDCS), a noninvasive form of neurostimulation, with potential for development as a self-administered intervention, has shown potential as a safe and efficacious treatment for OCD in a small number of trials. The two most promising stimulation sites are located above the orbitofrontal cortex (OFC) and the supplementary motor area (SMA).

**Methods:**

The aim of this feasibility study is to inform the development of a definitive trial, focussing on the acceptability, safety of the intervention, feasibility of recruitment, adherence and tolerability to tDCS and study assessments and the size of the treatment effect. To this end, we will deliver a double-blind, sham-controlled, crossover randomised multicentre study in 25 adults with OCD. Each participant will receive three courses of tDCS (SMA, OFC and sham), randomly allocated and given in counterbalanced order. Each course comprises four 20-min stimulations, delivered over two consecutive days, separated by at least 4 weeks’ washout period. We will collect information about recruitment, study conduct and tDCS delivery. Blinded raters will assess clinical outcomes before, during and up to 4 weeks after stimulation using validated scales. We will include relevant objective neurocognitive tasks, testing cognitive flexibility, motor disinhibition, cooperation and habit learning.

**Discussion:**

We will analyse the magnitude of the effect of the interventions on OCD symptoms alongside the standard deviation of the outcome measure, to estimate effect size and determine the optimal stimulation target. We will also measure the duration of the effect of stimulation, to provide information on spacing treatments efficiently. We will evaluate the usefulness and limitations of specific neurocognitive tests to determine a definitive test battery. Additionally, qualitative data will be collected from participants to better understand their experience of taking part in a tDCS intervention, as well as the impact on their overall quality of life. These clinical outcomes will enable the project team to further refine the methodology to ensure optimal efficiency in terms of both delivering and assessing the treatment in a full-scale trial.

**Trial registration:**

ISRCTN17937049. (date applied 08/07/2019).

Recruitment (ongoing) began 23rd July 2019 and is anticipated to complete 30th April 2021.

## Background

With a lifetime prevalence of 2–3%, obsessive–compulsive disorder (OCD) represents a leading global cause of functional disability [1, 2]. Affecting all population groups, regardless of gender and culture, OCD typically has an early onset, follows a prolonged course, and is associated with significant reduced quality of life (QoL) and social and occupational impairment [3]. Chronic OCD is associated with substantial comorbidity and considerable disability. The damage to psychosocial function is comparable to schizophrenia [3]. Severe OCD is associated with long-term hospitalisation, residential care and suicidal behaviour [4–8]. The economic impact of OCD to the individual, family and society is considerable in terms of direct and indirect costs [9]. Whereas evidence-based treatments lead to symptomatic improvement and associated improved QoL [10], rates of incomplete recovery and treatment resistance are high: approximately 40% patients do not respond, and 50% need further treatment [4]. Delayed treatment prolongs illness and reduces therapeutic gain [11]. New treatments are needed to improve health outcomes [12, 13].

Brain imaging demonstrates abnormal cortico-striatal neurocircuitry as underlying OCD pathology [14–17]. Studies show that targeting this circuitry with ablative neurosurgery and invasive neurostimulation with deep brain stimulation (DBS) improves OCD, possibly by enhancing information processing [4, 15, 18]. In 2009, DBS received the Food and Drug Administration (FDA) humanitarian use approval and the Conformité Européenne (CE) mark for the treatment of refractory OCD, making this disorder the first psychiatric indication approved for DBS treatment [19]. On the other hand, DBS is invasive, costly and burdensome and reserved for patients with severe, refractory OCD [15]. Noninvasive neurostimulation of superficial cortical nodes is safer and may potentially be applied earlier in the course of illness. Evidence from randomised controlled trials supports the efficacy of repetitive transcranial magnetic stimulation (rTMS) in OCD: meta-analyses have identified the orbitofrontal cortex (OFC) and supplementary motor area (SMA) as the most promising targets [20, 21]. In 2014, deep transcranial magnetic stimulation (d-TMS) was the first noninvasive neuromodulation treatment receiving EU marketing approval for the treatment of resistant OCD. However, TMS is also relatively costly, involves technical equipment and cannot be delivered in patients’ homes.

Transcranial direct current stimulation (tDCS) is an alternative noninvasive neurostimulation tool which involves administration of low-amplitude (1–2 mA) electric current to the brain between a cathode and anode. Anodal tDCS is thought to enhance cortical excitability and cathodal tDCS to have an inhibitory effect [22]. TDCS may be a preferable option as it is cheaper, portable, simple and safe to use [23]. Systematic reviews and meta-analyses indicate adequate safety, tolerability and potential efficacy in depression and other psychiatric disorders including OCD [22, 24–30]. The National Institute of Clinical Excellence (NICE) identified that the evidence on tDCS for depression raises no major safety concerns and encourage further research into tDCS [31].

Research into tDCS in OCD is still in its infancy. Preliminary evidence from small uncontrolled studies and case reports in treatment-resistant OCD patients confirm its safety and suggest encouraging efficacy results using protocols targeting OFC, SMA and other cortical regions (such as dorsolateral prefrontal cortex and dorsomedial prefrontal cortex) [22, 26–29, 32–34]. Studies present significant heterogeneity and methodological differences in sample selection criteria, concomitant treatment and tDCS stimulation protocols [22, 29, 33]. A randomised sham-controlled trial (*n* = 24 treatment-resistant OCD subjects) demonstrated efficacy for anodal tDCS administered over bilateral pre-SMA and cathodal tDCS over right supra-orbital regions [35]. However, a previous randomised crossover trial (*n* = 12) found clinical improvement with cathodal tDCS over pre-SMA, while anodal tDCS was ineffective [36]. Thus, replication studies are needed to determine the optimal stimulation protocol for tDCS over SMA in OCD. Another randomised, sham-controlled trial (*n* = 21 treatment-resistant OCD patients) using cathodal tDCS delivered over the OFC and the anode over the right cerebellum showed significant acute reduction of OCD symptoms immediately after the tDCS regimen compared with sham stimulation [37]. However, active tDCS was not superior to sham stimulation in alleviating OCD symptoms at the follow-up (12-week period) [37].

A recent double-blind, randomised, and sham-controlled study investigated the efficacy of tDCS as add-on treatment for treatment-resistant OCD (*n* = 43) [38]. Over 20 consecutive weekdays of active or sham tDCS sessions (30 min, cathode was positioned over the SMA and the anode over the left deltoid) were administered, followed by an 8-week follow-up. Patients that received active tDCS achieved a significant reduction of OCD symptoms than those that received sham at week 12, with mean (*SD*) Yale-Brown Obsessive–Compulsive Scale (Y-BOCS) score changes of 6.68 (5.83) and 2.84 (6.3) points, respectively (Cohen’s *d*: 0.62 (0.06–1.18), *p* = 0.03), with no between-group differences in responders (four patients in the active tDCS and one in the sham group) [38]. There were no significant effects in reducing symptoms of depression or anxiety, and patients in both groups reported mild adverse events [38]. Also based on theoretical and computational models, authors suggest that overall cathodal tDCS may be better than anodal in treating OCD patients with an extracephalic montage [23, 33].

## Method/design

### Aim

#### Primary objective

The main aim of this feasibility trial will be to inform the development of a subsequent definitive tDCS full-scale trial. This feasibility trial will collect information about recruitment, study conduct, tDCS delivery, and assessment methods to inform future trial design.

The objectives of this feasibility trial will be to assess:

•Acceptability and safety of the intervention

•Feasibility of recruitment

•Adherence and tolerability of tDCS and study assessments

•Willingness of clinicians to recruit participants

•Practicality of applying tDCS in the clinical setting

#### Secondary objectives

These clinical outcomes will enable the project team to further refine the methodology to ensure optimal efficiency in terms of both delivering and assessing the treatment in a full-scale trial.

•Optimal stimulation target (OFC, SMA)

•Likely magnitude of effect of the intervention on OCD symptoms, to determine standard deviation of the outcome measure, to estimate sample size

•Duration of effect of stimulation, to space treatments efficiently

•Usefulness and limitations of specific neurocognitive tests to determine a definitive test battery

Additionally, qualitative data will be collected from participants to better understand their experience of taking part in a tDCS intervention, as well the impact on their overall quality of life.

### Design

This feasibility study is designed as a double-blinded, sham-controlled, crossover randomised multicentre design in adults with OCD.

### Ethical approval

REC approval was granted to this study on 29th March 2019 (REC ref: 19/EE/0046). This study is co-sponsored by the University of Hertfordshire and Hertfordshire Partnership Foundation NHS Trust.

### Participants

**Table Taba:** 

Inclusion criteria	Exclusion criteria
• Community-based service users, aged 18 years or older. If the clinician has any concerns about the participant’s cognitive competence for the completion of the CANTAB assessment, a MoCA (Montreal Cognitive Assessment) will be conducted. Only those with no indication of cognitive impairment will be eligible. • DSM-5 defined obsessive–compulsive disorder determined by a research psychiatrist using the structured interview for DSM-5 • Duration of symptoms >1 year (from medical history) • Baseline score ≥ 20 on the Yale-Brown Obsessive–Compulsive Scale (Y-BOCS) • Ongoing medication (SSRI, tricyclic antidepressant, antipsychotic, benzodiazepine) is allowed as long as the dose is kept stable for a sustained period before (≥ 6 weeks) randomisation and remains so throughout the study. • CBT is not allowed during or within 6 weeks of the start of the intervention. • If patients have changed medication in the last 6 weeks or are receiving treatment already with CBT, they will need to return to the clinic after 6 weeks and then be randomised.	• History of psychotic disorder (schizophrenia, psychotic symptoms, bipolar disorder), Tourette syndrome (tic disorders not amounting to Tourette syndrome will not be exclusionary), organic mental disorder, psychosurgery, personality disorder of borderline or histrionic type • Alcohol/substance-abuse disorders within the past 12 months • Any other DSM-5 disorder that is considered the primary focus of treatment • Severe depression, defined by a Montgomery-Åsberg Depression Rating Scale (MÅDRS) score > 30 at baseline • Actively planning suicide (scoring > 4 on item 10 of MÅDRS) or judged by the clinician to be at significant risk of self-harm • Received CBT involving exposure response prevention (ERP) from an accredited (British Association of Behavioural and Cognitive Psychotherapies (BABCP) approved or equivalent) therapist (e.g. IAPTs stage 2) in the last 6 weeks • Highly CBT resistant (inadequate clinical response, equivalent to < 25% improvement); ≥ 3 previous adequate (> 12 weeks) trials of CBT involving ERP from an accredited (BABCP-approved or equivalent) therapist • Highly medication resistant (inadequate clinical response, equivalent to < 25% improvement); ≥ 3 previous adequate (> 12 weeks) trials of any SSRI or clomipramine taken at optimal doses with adequate adherence • Needing regular psychotropic drugs other than permitted medication. • Currently involved in a treatment research study • Acute or unstable physical illness • Skull defects, or skin lesions on scalp (cuts, abrasions, rash) at proposed electrode sites • History of surgical procedure with implanted body materials or devices (e.g. metal, pacemakers) • Epilepsy or other clinically defined neurological disorder or insult • Inadequate understanding of English to give informed consent or such that the outcome measurement is impossible • Women of child-bearing age not using reliable contraception (e.g. oral contraception pill, intrauterine contraceptive device or condom). • Pregnant or breast-feeding women

### Recruitment

Recruitment will primarily take place at 2 outpatient centres: Rosanne House (Welwyn Garden City, Hertfordshire Partnership University NHS Foundation Trust) and University Department of Psychiatry, College Keep, Southampton. Camden and Islington NHS Trust will also act as a Participant Identification Centre (PIC). It is expected that 200 patients will be screened to allow for recruitment of 25 patients (Fig. 1). This will provide a robust estimate of the ascertainment ratio for recruitment to the study (limits within ± 10%).

**Fig. 1 Fig1:**
[figure not shown]
Trial flow chart

Patients will be identified for screening from OCD clinics, primary health care services (e.g. Improved Access to Psychological Therapies (IAPTs)), charity/support networks, adverts/promotional material and Trust databases. Members of the research team will make regular contact with the relevant referring centres to ensure potential patients are referred. Trust databases will be screened for patients receiving routine care with a diagnosis of OCD. The research team will discuss their case with the treating clinician, and the clinician will refer the patient to the OCD service if deemed appropriate.

#### For patients referred from routine care to the OCD Service or the study

A member of the research team will identify adults with OCD who have been referred from routine care to the OCD Service (HPFT), or to the Mood and Anxiety Disorders Service (Southampton), or to the study, and will complete a screening log. The research team will either send the participant information sheet (PIS) about the trial or approach and provide this to the patient in the clinic and ask if they would be interested in taking part in the study. If agreeable, the patient will be sent a screening consent form and prepaid envelope. A clinician will be available to call the patient to discuss any queries that they may have. The patient will be asked to sign the consent form and post it to the research site; once received, the study clinician will arrange a convenient time to conduct the screening phone call. At the beginning of the screening phone call, the clinician will talk through the consent form with the patient to ensure that they have fully understood what they are consenting to, then countersign the signed consent form that had been sent by the patient.

#### For patients identified from primary health care services (e.g. IAPTs), charity/support networks, adverts/promotional material

OCD charity and support networks have given their support to the protocol and will advertise the study to their membership. Any patients who express an interest in the study will be sent information about the trial which will give a number to call to discuss further. Potential participants who respond to an advert or promotional material about the study will be sent information about the trial by one from the research team. Adverts/promotional material may be placed in primary health care services, health clinics attracting high levels of OCD patients, local newspapers, appropriate websites and relevant noticeboards. Research team members may also advertise the study through other media channels (e.g. local radio, patient support groups). Patients who express interest will be contacted by the researchers to discuss the study. If agreeable, a consent form and prepaid envelope will be sent. A clinician will be available to call the patient to discuss any queries that they may have. The patient will be asked to sign the consent form and post it to the research site, once received the clinician will arrange a convenient time to conduct the screening phone call. At the beginning of the screening phone call, the clinician will talk through the consent form with the patient to ensure that they have fully understood what they are consenting to, then countersign the signed consent form that had been sent by the patient.

#### For patients identified from the Trust databases

Patients who have a probable diagnosis of OCD on Trust databases will be identified by the clinical studies officers, research nurses, research assistants or research doctors. The treating clinician will be contacted and the suitability of the patient for the study discussed. If the treating clinician believes it is appropriate, the patient will then be referred to the study team for potential recruitment. Information about the trial will also be disseminated to clinicians. If they have suitable patients, they will refer them to the study team. The patient, if agreeable, will then be contacted by a member of the research team to see if they are interested in participating in the study. If interested, the patient will be sent an information sheet, consent form and prepaid envelope. A clinician will be available to call the patient to discuss any queries that they may have. The patient will be asked to sign the consent form and post it to the research site; once received, the clinician will arrange a convenient time to conduct the screening phone call. At the beginning of the screening phone call, the clinician will talk through the consent form with the patient to ensure that they have fully understood what they are consenting to, then countersign the signed consent form that had been sent by the patient.

### Screening

Patients will consent to be screened for the study. A member of the research team will assess eligibility according to the eligibility criteria and take a brief medical history. The results of all screening will be recorded both in the patients’ medical notes and on the study case report form (CRF). Eligibility criteria will be confirmed by the clinician who will be delivering the intervention.

### Randomisation scheme

Patients enrolled will be randomised to one of six permutations (4 per group):A—Sham: SMA: OFCB—Sham: OFC: SMAC—SMA: OFC: ShamD—SMA: Sham: OFCE—OFC: Sham: SMAF—OFC: SMA: Sham

The participant will sign the consent to study enrolment and randomisation. The clinician will have authorised access to the online randomisation programme. They will be provided with an identification code and password to access the randomisation programme. The clinician will enter the specific internet site, using their username and password and enter the study Patient Identification Number (PID), which includes the centre code. The computer will allocate the next consecutive randomisation allocation recorded automatically on the CRF. The clinician will record which intervention the patient was randomised to in the patients’ medical records and in a sealed envelope into the trial master file (TMF).

### Blinding

There will be two levels of blinding. The patient will be partially blinded as they will be able to tell which area is being stimulated (OFC/SMA), but they will not know whether it is sham/active stimulation as this will be preprogrammed. The RA doing the questionnaire outcome measures with patients will be fully blinded as they will not know the stimulation target or whether it is sham/active. In the event of an adverse event, the RA will report it to the clinician administering tDCS (unblinded) who will assess and manage it; patient unblinding will be considered if deemed appropriate.

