### Intervention

#### Preparation and labelling of the medical device

The HDCprog will be connected to the different HDCstimulators in the set-up phase of the study, and for each HDCstimulator will be defined the entire treatment application as per protocol, by setting the type of stimulation (active or sham), the intensity (2 mA) and the duration (20 min). Stimulation will take place in a quiet room. The patient sits awake in a comfortable chair. Electrodes are placed using the International 10–20 System [39]. The settings on the tDCS stimulator, marked with “1” and “2” codes known to the clinician responsible for the tDCS montage and delivery, are preselected for active or sham stimulation [40]. The clinician responsible for the montage will be instructed regarding the target site (OFC or SMA) by the external randomisation allocation. Intervention settings are unknown to the patient and the RA thus tDCS is administered in double-blind methodology. Individual sponge electrodes soaked in saline solution and standard EEG gel will be used. The active electrode is placed over the SMA (cathodal, Fz point) or left OFC (cathodal, FP1 point) and attached to the scalp using a personalised sterile head net tubular bandage. The inactive (reference electrode) is placed over the right deltoid using an elastic band. In active treatment, a 2-mA current is delivered for 20 min. Sham stimulation uses the same methodology apart from the current setting on the stimulator. Previous studies indicate that this procedure is well tolerated by participants with mental disorders, and reliability of sham procedures [24, 27, 28, 40–43].

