### Sample size calculation

Study sample size is evaluated with respect to the primary outcome (difference in the challenge Y-BOCS between tDCS and Sham), given that the aim is to estimate the likely effect size of a future trial. We assume that the sample will be representative of the population, and that the observed variance, and Y-BOCS scores in each condition will allow for estimation of a typical group comparison. Given that there are only 4 exposures of tDCS in each study condition, with 4 weeks between exposures, we assume no carry-over effects, which will be tested using a mixed model. Each tDCS target (OFC and SMA) will be considered independently against Sham. Published estimates of effect size vary widely [45]; thus, a conservative estimate of *d* = .3 is assumed. Following Cocks and Torgersen [51], assuming *α* = 0.05, 1 – *β* = 0.80, a sample size of 20 per group allows detection of a lower limit of *d*’ > 0.1 for an expected effect size *d*’ = 0.3. An additional 5 patients will allow for a 25% dropout.

It is estimated that approximately 25 patients will be recruited from a pool of 200 patients identified from screening, giving power to estimate the ascertainment ratio to within ± 6%. The proportion of missed treatment sessions is expected to be less than 20% from a total of 206 sessions, giving a precision within ± 6%. At the outset of the study, it is not possible to estimate the likely number of reported adverse events (safety), which is expected to be low, and cannot therefore estimate the likely precision of estimation.

Time-dependent changes in the Y-BOCS scores, and in the CANTAB test scores will be considered using standard paired comparisons (*t* test). A sample size of *N* = 20 allows for detection of an effect size *d*’ = .65 with power 1 – *β* = .78, and an effect size *d*’ = .77 with power 1 – *β* = .90. A time-dependent model will be evaluated (mixed model) to examine trends over time, but with limited power.

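### The six listed sequences give sham no site, and patients who can tell the site may infer one active course by course 3

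*Protocol article*

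**What the plan says.** The abstract's Methods paragraph states: "Each participant will receive three courses of tDCS (SMA, OFC and sham), randomly allocated and given in counterbalanced order". Under Randomisation scheme, patients are "randomised to one of six permutations (4 per group"). The list that follows contains every order of Sham, SMA and OFC, with sham as a single condition and no site attached.

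Stimulation schedules allows the sham course at either OFC or SMA. Preparation and labelling of the medical device says of the montage: "Sham stimulation uses the same methodology apart from the current setting on the stimulator". It also says: "The clinician responsible for the montage will be instructed regarding the target site (OFC or SMA) by the external randomisation allocation".

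The Blinding section calls the patient only partially blinded, because "they will be able to tell which area is being stimulated (OFC/SMA), but they will not know whether it is sham/active stimulation". The reason given for the second half is that the device is preprogrammed.

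Sample size calculation says: "Each tDCS target (OFC and SMA) will be considered independently against Sham". Likely effect size puts the main focus at 24 h after the last stimulation of each course.

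**The concern.** There are two linked problems.

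The first is masking. If a patient can see the site of each course, and every patient gets each site active once plus one sham, the pattern of sites carries information about which course is active. Preprogramming the stimulator does not hide that pattern. The information is one-sided: certainty can attach only to an active course, never to sham. Any expectancy effect would therefore tend to favour active stimulation. The Y-BOCS challenge, named as primary outcome in Sample size calculation, is a visual analogue scale meant for use by researchers or patients, so a masked rater does not remove patient expectancy.

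The second is the control. One sham course is compared with both targets, but it can share a site with only one of them. The listed sequences do not contain the sham site, so nothing shown fixes how often sham is same-site for OFC and how often for SMA. Choosing between the two targets is a stated secondary objective, and a lower limit for the effect size above 0.1 is one of the progression criteria.

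**Working it through.** **Inputs.** Three courses per patient (abstract, Methods); six orders, four patients each (Randomisation scheme); sham at OFC or SMA (Stimulation schedules); site recognisable to the patient (Blinding). The documents give no split of sham sites, so equal weight is an assumption.

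**The plan's own figure.** Orders of three conditions: 3! = 6. Patients: 6 × 4 = 24, against a recruitment target of 25. The difference of one has no bearing here.

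**Enumeration.** Cross the 6 orders with the 2 permitted sham sites: 12 cells.

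| Order | Sham at SMA: sites seen | Once-used site | Sham at OFC: sites seen | Once-used site |
|---|---|---|---|---|
| A Sham–SMA–OFC | SMA, SMA, OFC | course 3, active | OFC, SMA, OFC | course 2, active |
| B Sham–OFC–SMA | SMA, OFC, SMA | course 2, active | OFC, OFC, SMA | course 3, active |
| C SMA–OFC–Sham | SMA, OFC, SMA | course 2, active | SMA, OFC, OFC | course 1, active |
| D SMA–Sham–OFC | SMA, SMA, OFC | course 3, active | SMA, OFC, OFC | course 1, active |
| E OFC–Sham–SMA | OFC, SMA, SMA | course 1, active | OFC, OFC, SMA | course 3, active |
| F OFC–SMA–Sham | OFC, SMA, SMA | course 1, active | OFC, SMA, OFC | course 2, active |

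The once-used site is active in 12 of 12 cells. It is course 1, 2 and 3 in 4 cells each.

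**Probability that each course is sham, given the sites seen so far (equal cell weights).**
- After course 1 is set up: 1/3 for each course.
- Courses 1 and 2 at the same site (4 of 12 cells): 1/2, 1/2, 0. Course 3 is known to be active before it starts.
- Courses 1 and 2 at different sites (8 of 12 cells): 1/4, 1/4, 1/2. For example, OFC then SMA arises from A (sham at OFC), E (sham at SMA) and F (either site), where sham is course 1, 2, 3 and 3.
- After all three sites: 0 for the once-used site and 1/2 for each of the other two courses.

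In those 8 cells the certain course is course 1 or 2. It is identified only when course 3 is set up, weeks after that course's 24 h rating. Course 3 itself is then rated at even odds of being sham.

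**Range for the 4 in 12.** With equal numbers per order, the share is 2/6 whichever single site is used for sham, so one third holds for any split that is the same in every order. If the site depended on the order, the share could run from 0/6 to 4/6: orders A, B, D and E each have one sham site that puts the once-used site in course 3, while C and F have none.

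**Matching.** In every patient the sham is same-site for exactly one target. With an even split that is 24/2 = 12 patients per target, or 20/2 = 10 among 20 completers. If each site were a coin toss in 24 patients, the chance of a 16:8 or more uneven split is 2 × P(Bin(24, 0.5) ≥ 16) = 0.152, about 15%.

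**Data free of certainty.** Courses 1 and 2 contain both sham and OFC only in B and E, and both sham and SMA only in A and D: 2 × 4 = 8 of 24 patients per target. C and F contribute none.

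**The case against.** The Blinding section does not claim full masking: it says the patient is partially blinded. That stands as disclosure that the site is known. It does not cover the consequence, because the same sentence goes on to say that sham and active will not be distinguished.

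A reader might infer that the unblinded clinician chooses the sham site. The document does not support that. It says the clinician "will be instructed regarding the target site (OFC or SMA) by the external randomisation allocation", with no exception for sham, and the article condenses a fuller protocol. What remains is that the listed sequences and this sentence do not agree and need reconciling.

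A reader might also infer that patients can unmask the sham, or both active courses. The enumeration shows otherwise: one active course becomes certain, and the other two remain at 50:50.

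The deduction also requires patients to know that they receive each site active once plus one sham. That depends on the information sheet, which is not shown. The questionnaire outcomes are collected by a research assistant masked to both site and activity. Nothing in the document shows that sham response differs by site, so no size can be put on the bias from an other-site sham. All of this stands and limits the size of the problem. None of it makes the blinding statement correct.

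**Conclusion.** The point holds in a limited form. The statement that patients will not know sham from active is wrong for one course per patient, provided they know the three-course structure. Certainty precedes the 24 h rating of the course concerned in 4 of 12 cells, under an equal sham-site split. In the other 8 it comes after that rating.

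Separately, sham site is absent from the listed sequences, and nothing shown balances it across the two contrasts that share the single sham course.

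It would go too far to conclude that the effect size is invalid or that this bias decides progression. Progression to a full trial rests on all findings, including ascertainment, refusals and recruitment, and the clinical effect is a secondary analysis. The planned sample size is not affected. The change is still worth making, because it is cheap and protects both target-versus-sham contrasts.

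**What to change.** 1. Reconcile Randomisation scheme, Preparation and labelling of the medical device, and Stimulation schedules on how the sham site is set.
2. For remaining allocations, have the randomisation issue the sham site, balanced within each of the six orders. Record the site actually used for patients already treated.
3. Add sham site (same-site or other-site) to the mixed model for the target-versus-sham contrasts. Code it as a property of the sham course, because a patient-level covariate would largely cancel from a within-patient contrast.
4. Restate the Blinding section to say that one active course may become inferable by course 3, and report the effect size with that caveat.
5. Optional: one allocation guess per course, and a sensitivity analysis without course 3 ratings. With about 8 of 24 patients per target, the latter can only be descriptive.

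The cost is a revised allocation list and one extra model term, which will be imprecise at 10 to 12 patients per sham site. Balancing the sham site settles the matching but leaves the deduction in place: the once-used site would still be active in all 12 combinations. The corrected wording and the caveat are therefore needed as well.
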